### Blinding

Due to the nature of the intervention, this is an open-label trial; treatment are assigned blindly by the randomisation software, but the trial staff involved, including data analysts, were aware of the arm allocation for each patient. Caretakers and study personnel are aware of the study arm allocation for participating children due to the differences in anthropometric criteria and RUTF ration. On inclusion, the nurse research officer gives each trial participant’s caretaker a card specifying the nutritional strategy being followed by the child. Caretakers are asked to present this card in the event of an unplanned outpatient consultation or hospital admission during the study period. In this way, nurses or doctors at any health facility are able to identify the nutritional treatment being followed by the child.

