### Study outcomes

The primary outcome will be judged by a binary composite indicator. Children classified as “favourable outcome” fulfil all of the following criteria: alive, not acutely malnourished per the anthropometric definition applied at inclusion (MUAC > 125mm and WHZ > − 3, and no oedema) and not having an additional episode of AM throughout the 6-month observation period. This outcome is measured at 6 months after randomisation. All other children are classified as “unfavourable outcome”.

The main secondary outcome #1 will be determined among children who meet the current WHO definition of SAM at inclusion (MUAC < 115 mm or WHZ < − 3 or oedema +, ++). The main secondary outcome #2 will be determined among children admitted with a MUAC < 115mm or oedema (+, ++). For these two subgroups, recovery is defined in each arm by a 4-week minimum duration of treatment, an axillary temperature < 37.5 °C, and an absence of bipedal oedema and a MUAC ≥ 125 mm for two consecutive weeks. This outcome is measured throughout the 6 months post-randomisation, meaning a child will be considered as recovered if he reaches these criteria during the 6-month follow-up in outpatient or village visits. Additional secondary outcomes are listed in Table 1.

**Table 1 Tab1:** Primary and secondary outcomes in the OptiMA Niger trial

	Measurement variable	Method of aggregation	Time point

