**Main secondary**			
Recovery	Composite: absence of bipedal oedema and a MUAC > 125 mm for two consecutive weeks, a 4-week minimum duration of RUTF treatment, and a good clinical health (without fever)	Proportion	Throughout the 6-month follow-up period
**Secondary**^a^			
Cost-effectiveness	Incremental cost-effectiveness ratio (ICER)	Ratio	Throughout the 6-month follow-up period
Consumption of RUTF per children with a favourable outcome	Sachets of RUTF consumed	Mean	6-month post-inclusion
Consumption of RUTF per recovered children	Sachets of RUTF consumed	Mean	End of RUTF treatment initiated at inclusion
Average daily weight gain in SAM children recovered	g/kg/day	Daily	End of RUTF treatment initiated at inclusion
Average daily MUAC gain in SAM children recovered	mm/day	Daily	End of RUTF treatment initiated at inclusion
Hospitalisation	Children with at least one episode of hospitalisation	Proportion	Throughout the 6-month follow-up period
Relapse to a new episode	Children with MUAC < 125 or WHZ < − 3 *Z*-score or oedema after RUTF treatment	Proportion	After recovering from the first episode of acute malnutrition
Non-response	Children who did not reach the recovery criteria	Proportion	16 weeks after inclusion
WaST	Children associated with severe and moderate stunting with acute malnutrition	Proportion	Throughout the 6-month follow-up period

^a^All the secondary outcomes will be analysed for the overall population (MUAC < 125 mm or WHZ < − 3 or oedema) and for the secondary populations (SAM WHO and MUAC < 115 mm or oedema)

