### Statistical analysis

All statistical analyses will be performed using the RStudio Software (Boston, MA, USA) as specified by the data analysis plan published on ClinicalTrials.gov prior to performing any analysis. Statistical tests will be carried out bilaterally with an alpha risk of 5% and unilaterally with an alpha risk of 1.25% for the non-inferiority analysis. Qualitative variables will be described in terms of numbers and percentages and provided with CIs when relevant. If necessary, comparisons of qualitative variables will be made using *χ*^2^ or Fisher exact tests. Quantitative variables will be described in terms of mean, SD, and CI or median, range, and IQR. If necessary, comparisons of quantitative variables will be made using Student’s, Wilcoxon’s, or Kruskal-Wallis tests, depending on the distribution of the variable of interest. Time delay type variables will be described in terms of the incidence of occurrence, and the probability of occurrence over time, estimated by the Kaplan-Meier method. If necessary, probability comparisons will be made using log-rank tests, or proportional risk models, after verification of the assumption of proportionality of risks.

The main analysis of the primary and secondary outcomes will be intention-to-treat and per-protocol given that this is a non-inferiority trial. Participants included in the main analyses will be described according to the diagram defined by CONSORT (Consolidated Standards of Reporting Trials) recommendations [18]. The occurrence of the primary “favourable outcome” and the secondary main outcome “recovery” will be compared between the two randomisation arms. These two comparisons will be performed both by “intention-to-treat” basis and on a “per-protocol” basis. Non-inferiority analyses will be performed on these two outcomes. Only if non-inferiority for these two outcomes is demonstrated will the other secondary analyses will be performed and, if appropriate, as a superiority analysis. Superiority will be particularly sought for cost outcomes related to RUTF cost-efficiency.

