### Safety

The trial is monitored monthly by an international steering committee and twice a year by a national steering committee where any adverse events are presented. We also planned a field visit by the national steering committee during the enrolment phase. The data safety and monitoring board (DSMB) for this trial did not request any interim analysis, but security analyses are planned after 500 and 1500 inclusions and will consist in comparing across study arms mortality, hospitalisation, and life-threatening events rates. The DSMB will meet at least twice during the recruitment phase to make recommendations following the security analysis. The ethics committees did not require any meetings during the active phase.

A child included in one of the two intervention arms could be removed from the study if (s)he experiences two consecutive episodes of > 5% weight loss during the course of treatment and is hospitalised once, or if (s)he is not SAM at inclusion but deteriorates to SAM during RUTF supplementation.

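### Data analysts know each child's arm for a reason that covers only caretakers and clinic staff, leaving an avoidable route for arm-dependent calls on outcome derivation and per-protocol membership

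*Protocol article*

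**What the plan says.** The Blinding section opens with "Due to the nature of the intervention, this is an open-label trial" and then says that "the trial staff involved, including data analysts, were aware of the arm allocation for each patient". It explains the awareness of caretakers and study personnel by the differences in anthropometric criteria and RUTF ration. It gives no separate reason for the analysts.

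Under Statistical analysis, "The main analysis of the primary and secondary outcomes will be intention-to-treat and per-protocol given that this is a non-inferiority trial". The same section says that analyses will be run "as specified by the data analysis plan published on ClinicalTrials.gov prior to performing any analysis".

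One component of the primary outcome, in Study outcomes, is "not having an additional episode of AM throughout the 6-month observation period". Table 1 gives numeric thresholds (MUAC, WHZ or oedema, after RUTF treatment) for a secondary outcome, "Relapse to a new episode".

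The Safety section allows removal from the study for children in the two intervention arms under stated conditions of deterioration. It states no such provision for control. It also says that "security analyses are planned after 500 and 1500 inclusions and will consist in comparing across study arms mortality, hospitalisation" and life-threatening events.

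**The concern.** An open-label trial can still have masked data handling. Children, caretakers and nurses cannot be masked to sachets of food, but the person who programs the outcome or decides who belongs to the per-protocol set can work without the arm label for most of that task. The article states the opposite as a design choice, so this is not detail left to an unseen analysis plan.

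It matters more here than in a superiority trial. If children who fail are left out of an experimental arm's per-protocol set, that arm's success rate rises and the result moves towards non-inferiority. The removal provision applies to the intervention arms only and concerns children who are doing badly. Whether they count in the per-protocol set is therefore exactly the kind of decision that should not be made with the arm and the outcome both in view. Rulings on episodes or on borderline measurements would also reach the intention-to-treat result.

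**Working it through.** **1. Is the stated reason sufficient?** The Blinding section's reasons concern what is visible at the point of care. Analysts do not handle rations or measure children. The reason does not extend to them.

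**2. Where could judgement remain?**
- *Per-protocol membership.* It can turn on ration received, discharge on the arm's own criteria (Follow-up: WHZ is required only in the standard arm), defaulting (a numeric rule: three consecutive absences), and removal (Safety: intervention arms only).
- *Further episode.* Table 1's relapse rule starts after RUTF treatment and recovery. Control children aged 24–59 months with moderate malnutrition receive no supplementation (Intervention), so for them that rule has no obvious starting point. Non-responders leave treatment unrecovered at 16 weeks.
- *Boundary value.* The outcome text and Table 1 use MUAC above 125 mm; the recovery text, Table 2 and the exit criteria use 125 mm or more. A reading of exactly 125 mm needs a ruling.

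**3. The plan's own sample size, to anchor the illustration.** Inputs from Sample size and Statistical analysis: 68% in each arm, margin 10 points, one-sided alpha 1.25%, power 90%, inflation 5%.

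n = (2.2414 + 1.2816)² × 2 × 0.68 × 0.32 / 0.10² = 541 per arm; 541/0.95 = 570. A restricted-variance version gives 539, then 568, which is the stated figure. The inputs are therefore read correctly.

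**4. Extreme bound for per-protocol exclusions.** Expected successes per arm: 0.68 × 568 = 386.2.
- Drop 1% of one arm, all failures: 386.2/562.3 = 68.7%, a rise of 0.7 points.
- Drop 5% (28.4 children), all failures: 386.2/539.6 = 71.6%, a rise of 3.6 points.
- Drop 5%, half of them failures: (386.2 − 14.2)/539.6 = 68.9%, a rise of 0.9 points.
- Drop 5% with the arm's own 32% failure rate: no change.

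Each case assumes that exclusions fall in one arm only.

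**5. What a net reclassification would do to the error rate.** Assumption: 540 evaluable children per arm. At 68% in both arms, SE = √(2 × 0.68 × 0.32/540) = 2.84 points and the half-width is 2.2414 × 2.84 = 6.4 points. Non-inferiority is then shown up to an observed deficit of 10 − 6.4 = 3.6 points, about 20 children. (That this equals the 3.6 in step 4 is coincidence.)

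At a true 10-point deficit (68% against 58%), SE = √((0.2176 + 0.2436)/540) = 2.92 points and the type I error is Φ(shift/SE − 2.2414):

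| Net children turned favourable in one arm | Shift (points) | Type I error |
|---|---|---|
| 0 | 0 | 1.25% |
| 5 | 0.9 | 2.7% |
| 11 | 2.0 | 6.1% |
| 16 | 3.0 | 11.0% |
| 27 | 5.0 | 29.8% |

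These figures show how sensitive the test is. They do not estimate how many such calls would be made.

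**The case against.** The strongest reply is that the decisions may already be fixed. The analyses follow a plan to be published before any analysis, and that plan may well define the per-protocol set and the episode rule. This stands. A reader might infer from the article that these matters are still open; the documents do not show that, and their absence from a condensed article is not a fault. What the reply does not settle is timing: before any analysis is not the same as before the analysts knew the allocation.

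Second, most of the classification is numeric (vital status, MUAC, WHZ, oedema, three missed visits), so the room for discretion is narrow. This largely stands, subject to the gaps in step 2 of the working.

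Third, intention-to-treat runs alongside per-protocol, and per-protocol exclusions cannot change it. A distorted per-protocol set would show as a discrepancy between the two. This stands for set membership, but not for episode or boundary rulings, which enter both analyses.

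Fourth, coded arms would not hide everything. Non-randomised children with WHZ below −3 and MUAC of 125 mm or more exist only in control (Eligibility criteria). So do unsupplemented moderate cases aged 24–59 months, who are followed at home from the start (Follow-up). And adherence cannot be judged with ration and exit data withheld. All of this stands, so it would be wrong to say that coding prevents the problem at no cost.

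Finally, a reader might infer that the two security analyses show outcomes by arm to the final analysts. The article does not say who runs them and shows no link to episode or per-protocol decisions.

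**Conclusion.** The point holds in a limited form. The article leaves analysts aware of allocation on grounds that do not apply to them, in a trial where per-protocol is a main non-inferiority analysis and removal from the study is stated only for the intervention arms. The pre-published plan, the numeric rules and the parallel intention-to-treat analysis reduce the exposure but do not close it.

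The 3.6-point figure is only an extreme bound, needing 5% of one arm excluded, every one a failure, and none excluded elsewhere. The error-rate table rests on an assumed 540 evaluable children per arm and on hypothetical counts. Nothing in the documents indicates that any arm-dependent decision was made. This is a cheap improvement to the safeguards and does not show the results to be biased.

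**What to change.** Amend the Blinding section so that the open-label reason is confined to caretakers and clinic staff, and state how the data are handled:

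- Outcome and episode derivation is programmed and locked on a dataset with arm labels removed or coded, and with the control-only non-randomised children held apart.
- Per-protocol membership is set by a pre-written rule applied by program, using ration and exit data where adherence requires them, or by people who have not seen outcomes by arm. It is locked before the arm key is merged for the comparison.

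The article puts the end of follow-up at June 2022, after its own publication in January 2022, so on its own dates this could still be done before the final comparison.

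The cost is one data-management step, with no change to enrolment, treatment or sample size. The limit is that masking is partial, because visit and ration patterns can reveal the arm. It also does nothing about measurement by unmasked field staff, which is a separate matter.

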### Children selection procedure and enrolment

Prior to enrolment, the research team composed of community health workers (CHWs), nurses, clinical trial technicians, clinical trial monitors, data mangers, and Ministry of Health (MoH) medical staff implicated in the study were trained on the trial protocol, standardised operating procedures (SOP), and the correct use of IT tools developed for data collection. Clinical trial technicians were specifically trained to enrol and randomise study participants and to monitor home visits and outpatient visits at the health centre. Due to the SARS-Cov-2 pandemic, all staff were also trained on barrier measures (wearing a mask, physical distancing, interviewing outside, washing hands).

Children are directly recruited when they presented for outpatient consultation in one of the four health centres selected in the trial. To ensure the data quality required in a randomised controlled trial and to cover the AM peak (July to October), we control the number of inclusions per day. A maximum threshold is fixed at 7 inclusions per day and per clinical trial technician. When more than 7 children are eligible per day in a health centre, a standard operating procedure to ensure a random selection of children is implemented. Mothers with their children are used to arriving early at the health centre. MoH staff in charge of the screening at admission give a numbered card to the mother if the child is eligible for the trial (anthropometric criteria, age, and place of residence). Once most of the mothers have arrived, the research field coordinator is informed by phone of the number of eligible children and proceeds to the randomised selection of children from numbered balls in a bag. The following data on age, sex, MUAC, WHZ, and distance between the village and the health centre are collected for all eligible children to check on the representativeness of the sample. Children randomly selected are proposed to participate to the trial, and the others do not participate in the trial and follow the standard protocol.

During the screening at health centres, a MoH staff supervised by a clinical trial technician collects the anthropometric (weight, height, MUAC, WHZ), demographic (age, sex), and clinical (oedema) data on eligible children. A standard operating procedure for assessing child anthropometry (weight, height, MUAC, and oedema) is observed at each site (see Additional file 2). Then, children undergo a medical consultation to determine whether they meet the inclusion criteria.

### Informed consent procedure

For each eligible and selected child, the caretaker is given a study information sheet explaining the study’s aims, treatment protocols, study duration, and frequency of clinic visits and community follow-up. On the consent form, participants will be asked if they agree to the use of their data should they choose to withdraw from the trial. Participants will also be asked for permission for the research team to share relevant data with people from the universities taking part in the research or from regulatory authorities, where relevant. This information is explained orally in Haoussa (local language). Caretakers who agreed to participate in the study indicate their consent by signing (signature or fingerprint) a written consent form. When caretakers are not able to read or write, an impartial witness oversaw the consent process and attest to the caretaker’s consent by signing the consent form on her/his behalf. All caretakers are informed about their right to withdraw from the study at any time without affecting the quality of medical care provided to their children. All medical care and nutritional treatment are provided free of charge, regardless of participation in the study. This trial does not involve collecting biological specimens for storage.

### Intervention

Table 2 summarises the difference in treatment eligibility, recovery definition, and exit criteria between the current national protocol in Niger, OptiMA, and ComPAS strategies. The RUTF ration per week according to standard, OptiMA, and ComPAS strategies are detailed in Additional file 3.

**Table 2 Tab2:** Wasting definition, treatment products, calculation of dosage, and recovery definition in the Niger national, OptiMA, and ComPAS protocols

	National Niger protocol			OptiMA protocol			ComPAS protocol	
	SAM	MAM		Acute malnutrition			Acute malnutrition	
*Wasting definition*	MUAC < 115 mm or WHZ < − 3 or bipedal oedema	MUAC (115–124 mm) or − 3 < WHZ < − 2 and without bipedeal oedema		MUAC < 125 mm or bipedal oedema			MUAC < 125 mm or bipedal oedema	
				MUAC < 115 mm or bipedal oedema	MUAC 115–119 mm	MUAC 120–124 mm	MUAC < 115 mm or bipedal oedema	MUAC 115–124 mm
*Treatment product and quantity*	RUTF 150–200 kcal/kg/day	If aged 6–23 months: super cereal plus 200 g/day (~ 787 kcal/day) or RUSF, one 92 g sachet/day (500 kcal/day)	If aged 24–59 months: no supplementation	RUTF 170–200 (kcal/kg/day)	RUTF 125–190 (kcal/kg/day)	RUTF 50–166 (kcal/kg/day)	RUTF 1000 kcal/day (2 sachets/day)	RUTF 500 kcal/day (1 sachet/day)
*Calculation of dosage*	According to the weight	Fixed amount, regardless of weight or MUAC status	–	According to MUAC status and weight			According to MUAC status	
*Frequency*	Weekly	Weekly	No visit	Weekly	Weekly	Weekly	Weekly	Weekly
*Recovery definition*	• MUAC ≥ 125 mm AND WHZ ≥ − 2 for 2 consecutive weeks • No oedema for 14 days • 4 weeks of participation in the programme • Good clinical health (no fever)			• MUAC ≥ 125 mm for 2 consecutive weeks • No oedema for 2 consecutive weeks • 4 weeks of participation in the programme • Good clinical health (no fever)			• MUAC ≥ 125 mm for 2 consecutive weeks • No oedema for 2 consecutive weeks • 4 weeks of participation in the programme • Good clinical health (no fever)	

*ComPAS* Combined protocol for Acute Malnutrition Study, *MAM* moderate acute malnutrition, *MUAC* mid-upper arm circumference, *OptiMA* Optimising acute MAlnutrition, *RUSF* ready-to-use supplementary food, *RUTF* ready-to-use therapeutic food, *SAM* severe acute malnutrition, *WHZ* weight-for-height *Z*-score

In the control arm, children included with a MUAC < 115 mm and/or WHZ < − 3 and/or nutritional oedema are treated weekly with RUTF, according to the Niger national protocol dosage table based on the child’s weight. The Niger protocol provides a RUTF daily caloric intake of 150–200 kcal/kg/day during the entire treatment schedule until recovery in children with SAM. Children under 2 years old included with a MUAC between 115 and124 mm and WHZ > − 3 without bipedal oedema are treated weekly by one sachet of RUSF per day (500 kcal/day) during the course of treatment. However, children over 2 years old meeting the same moderate anthropometric criteria are not eligible for supplementation according to the national MAM programme.

The simplified strategies apply to AM children defined as MUAC < 125 mm or bipedal oedema (+, ++) without medical complications on admission and with a good or moderate appetite test.

In contrast to the weight-based RUTF ration in the national SAM programme, the OptiMA RUTF ration is calibrated to the child’s degree of wasting based on the combination of MUAC status and weight. Thus, more nutritional support is given to the most severely malnourished children and then gradually reduced as the child’s MUAC increased. Children with MUAC < 115 mm or oedema receive 175 kcal/kg per day of RUTF. Children with MUAC 115–119 mm, either at admission or during the course of treatment, receive 125 kcal/kg per day of RUTF, and children with MUAC ≥ 120 mm receive 75 kcal/kg per day of RUTF (with a minimum of one sachet/day) until discharge from the programme.

The ComPAS strategy is the most simplified protocol, not requiring a dosage table and proposing to gradually reduce the dosage according to the child’s MUAC status only during the outpatient follow-up as follows: 2 sachets/day of RUTF to children with MUAC < 115 mm or oedema and 1 sachet/day for children in the 115–124 mm MUAC zone.

For both simplified strategies, children with oedema receive the same RUTF ration as children with MUAC < 115 mm until oedema are resolved, at which point their ration is determined by MUAC and weight.

All other aspects of the standard nutrition protocol are similarly applied to all children in the three arms. All children undergo malaria rapid testing upon admission and at any point during their participation if clinical signs of malaria are detected. All children with positive malaria rapid diagnostic test are prescribed an artemisinin combination treatment. Amoxicillin 50–100 mg/kg/day is prescribed for 7 days to all SAM children. Seasonal chemoprevention (SCP) campaigns were organised by the MoH during the malaria pic (July to October). Albendazole or mebendazole is given to children who are at least 12 months old and did not get deworming in the previous 4 months. Children who did not have all the recommended vaccines up to date were vaccinated especially the measles vaccine. Children requiring higher-level treatment are referred to the inpatient facility in Mirriah or at Zinder Hospital. Hospitalisation criteria and treatment procedures follow the national recommendations in Niger.

